### 2.9. Ethics and dissemination

The study has been approved by the Ethical Committee of Dongzhimen Hospital, and ethical approval will be obtained from the local ethics committees of the other centers. The amended version of the protocol will then be published to the Chinese Clinical Trial Registry after receiving ethical approval for any modifications. The study will be conducted per the Helsinki declaration, in which patients must provide written informed consent before participation. The study results will be published in national and international peer-reviewed journals and presented at scientific conferences. We plan to communicate our findings to potential or diagnosed AHF patients and their families to help them understand the risks and benefits of drug use.

## 3. Discussion

This is the first large prospective cohort study to evaluate the Chinese herbal injection effectiveness in AHF patients. This Chinese herbal injection, YQFM, is being studied in large RCTs such as AUGUST-AHF and applied clinically to treat AHF. Although the data from RCTs could provide critical evidence of clinical activity, the strict eligibility criteria may raise concerns about generalizability. Therefore, it is essential to evaluate the effectiveness of YQFM in a real-world study.

### 3.1. Drug rationale

Yiqi Fumai lyophilized injection is accepted by most patients in China because of its effectiveness and safety, and can be used as an important supplementary drug for HF treatment. At a pathophysiological level, YQFM improves coronary blood flow, reduces myocardial oxygen consumption, inhibits inflammatory mediators, and reduces myocardial injury (24). The potential mechanism may be multifactorial. At a molecular level, it could improve cardiac tissue damage and fibrosis and reduce the serum levels of BNP, CK, LDH, and hs-CRP (25, 26). It has also been discovered to improve the mitochondrial function of cardiomyocytes by regulating mitochondrial biogenesis-related proteins and inhibiting apoptosis while attenuating cardiac hypertrophy by autophagy regulation through the PI (3) K/AKT/mTOR pathway (11, 27).

Furthermore, YQMF attenuates doxorubicin-induced cardiotoxicity, hepatotoxicity, and nephrotoxicity in rats by oxidative stress inhibition, inflammation, and apoptosis (28). In a meta-analysis of 33 RCTs (10), YQFM combined with standard HF therapy was reported to have a significantly higher likelihood of improving treatment response. According to reports, YQFM considerably improved heart function, the performance of the 6-Minute Walk Test, and the patient’s quality of life, as well as lowered NT-proBNP levels. The AEs and clinical safety of YQFM has been well documented and assessed in previous studies. Potential adverse effects of YQFM mainly include pruritus, rashes, nausea, palpitations, and drowsiness, and most of them were remitted after treatment (10, 29). Safety surveillance studies with large sample sizes have been performed, which reported low incidence of AEs from 0.176 to 1.25% (29–31). Several systematic reviews of RCTs also reported that an acceptable safety profile (10, 32, 33). Overall, YQFM has been demonstrated to be safe, with very low incidence of AEs.

### 3.2. Exposure rationale

#### 3.2.1. Endpoints and outcome measures rationale

Since patients are prone to recurrence with exacerbation and have a high risk of death and readmission during the vulnerable 90 days after HF hospitalization (34, 35), we focused on this 90-day composite endpoint, a high-risk period for AHF patients that require special attention and close follow-up (36, 37). Besides, evidence has shown that HF patients’ vital signs (e.g., heart rate) and medication adherence after discharge are prognostic factors (38–40). However, many efficacy studies of pharmacological interventions have neglected this association and have not collected this data. Therefore, we used the smartwatch and app to collect information on vital signs and medication adherence during follow-up. Meanwhile, patients might be remotely monitored through the app to save time and money on unnecessary travel. The use of smartwatches could better monitor patients’ health conditions. Innovative models of remote monitoring based on technological advances may help overcome the challenges of long follow-up management for patients and reduce shedding rates.

#### 3.2.2. Study design rationale

In our study, we will apply a broader eligibility criterion and nearly the same outcome measures as the AUGUST-AHF RCT study (shown in Tables 1, 2). The study results will represent the long-term effectiveness of YQFM in a real-world setting.

Furthermore, we will compare the population and results of our study with the AUGUST-AHF RCT study. Complex patients with multimorbidity or a history of specific treatments, like heart transplantation, will be excluded from the AUGUST-AHF RCT investigation, raising concerns regarding the trial’s generalizability and the unknown benefit and risk of Yiqi Fumai Lyophilized Injection for this group. In our study, we specifically set up an assessment to determine whether patients are eligible for the AUGST-AHF RCT study. By comparing the populations of the two studies, we could determine the representativeness of the AUGUST-AHF RCT study populations to real-world patients and describe differences in the characteristics of patients who met the RCT eligibility criteria and those who did not participate in a real-world setting, something that is rarely mentioned in existing studies. Those who do not meet the AUGUST-AHF eligibility criteria will be analyzed separately to obtain efficacy in an underrepresented population.

Some studies have demonstrated that the outcomes of patients in clinical trials differ from those in real-world settings, with lower survival rates and a higher incidence of AEs (13, 14). The results of our study will be compared with AUGUST-AHF to verify whether this condition also exists in HF patients and to analyze its possible causes. The outcome measures are largely the same between the two studies, facilitating data comparability. Furthermore, differences in compliance between trial and non-trial patients have been cited as an important reason for differences in results (39). Thus, we will include compliance analysis as an important part of the study to explore the differences in compliance between patients in and out of clinical trials and their impact on clinical outcomes. The study outcomes will aid patients, physicians, and policymakers in selecting the optimal treatment options for all patient subgroups. The method could potentially serve as a model for utilizing RCT-validated data in routine clinical practice.

In this cohort study, it was nearly impossible to remove biases. First, participating centers are all tertiary hospitals. Thus, referral bias could be present. Considering AHF as a serious to life-threatening acute disease, patients with suspected AHF are almost exclusively referred to tertiary hospitals in China, and few patients are left in community hospitals. This may weaken the impact of referral bias. Moreover, propensity score methods will balance the two cohorts’ baseline characteristics, avoiding selection bias. Second, the study will involve numerous patient assessments, and both the proficiency of the assessors and the way of questioning may affect the assessment’s reliability, leading to measurement bias. Therefore, we will conduct uniform training for the assessors to avoid it. Third, telemedicine and telemonitoring (the smartwatch and app) may reduce mortality and readmission, resulting in confounding bias. However, in this study, both the exposed and the non-exposed group will be set up with the same telemedicine and telemonitoring, which may eliminate the influence of this confounding factor.

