### 2.4. Outcomes

The primary outcome is a composite of 90-day all-cause mortality or readmission for HF. The secondary outcomes are 180-day all-cause death or HF readmission, cardiac-specific death, major cardiovascular adverse event (MACE), length of hospital stay, dyspnoea by visual analog scale (VAS), dyspnoea by Likert 7-point scale, New York heart association (NYHA) cardiac function classification, Minnesota Living with Heart Failure Quality of Life (MLHFQ) scale, and Morisky Medication Adherence Scale (MMAS)-8. The cardiac-specific death is defined as death due to myocardial infarction (MI), worsening heart failure, death due to cardiovascular procedures, or other cardiovascular causes. MACE is defined as any of the following: death, MI, stroke, hospitalization because of HF, and revascularization, which includes percutaneous coronary intervention and coronary artery bypass grafting.

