### 2.5. Study assessment

Researchers will assess patients daily during their hospitalization until their discharge and at the follow-up (details shown in Table 2). After patients have been enrolled in this study, researchers will examine their eligibility for the AUGST-AHF RCT study. The use of YQFM will be evaluated based on the daily medication record. The MACE endpoints and cardiac-specific death will be assessed and determined by the endpoint committee. VAS and 7-point Likert scale will be used to assess dyspnea by patient self-report, and the two scales will be measured at approximately the same time in patients’ supine position to ensure consistency. The MLHFQ scale consists of 21 questions and has been widely used to assess HF patients’ life quality (17). The Chinese version of MMAS of eight items has been extensively validated in China (18). It shows reliability and validity for HF patients (19), which would be a suitable tool for our study to assess patients’ medication adherence. Adverse events (AEs) will be monitored until Day 10 or until patients are discharged and significant AEs until Day 180.

**TABLE 2 T2:** The schedule of assessment and data collection.

	Baseline	During the patient’s hospitalization^1^										Follow-up			
**Time point**	**Day 0**	**Day 1**	**Day 2**	**Day 3**	**Day 4**	**Day 5**	**Day 6**	**Day 7**	**Day 8**	**Day 9**	**Day 10**	**Day 30**	**Day 60**	**Day 90**	**Day 180**

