#### 2.6.2. Follow-up

Following enrolment, patients will be monitored for a minimum of 180 days, with visits occurring at 30, 60, 90, and 180 days. During follow-up, we will use a smartphone-based clinical reporting application (app) to manage patients. Patients will fill out the MLHFQ and MMAS-8 scales online by this app. Before discharge, the doctor will explain the details of the app’s scales to patients and their relatives until they fully understand. Concurrently, the app will display essential discharge instructions and details. Within seven days of each visit time point (30, 60, 90, and 180 days), an independent investigator will confirm survival status, HF readmission, NYHA cardiac function classification, MACE, and AEs of patients by telephone or outpatient, and remind patients to complete the app questionnaire in the app. We will provide patients with smartwatches and ask them to wear these smartwatches during follow-up, which could monitor their body weight, BP, and heart rate. The records will be automatically uploaded to the app through Bluetooth. All data will be sent over the internet to a back-end infrastructure on secure servers. Moreover, this specially designed app gives researchers secure online access to scale information and patients’ vital-sign readings.

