### 2.7. Sample size

Based on the results of previous observational studies, the composite outcome of 90-day all-cause mortality or readmission for HF was approximately 25% among patients who received conventional therapy for acute heart failure (20, 21). We assumed that the composite rate of those who combined with YQFM in clinical practice is 18%. Setting a significance level of two-sided alpha level of 0.05 and 10% of the loss to follow-up, 1,200 patients would be enough to detect the composite outcome with 80% power.

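### Uniform assessor training improves reliability but does not prevent outcome judgement that differs by known YQFM exposure, and neither the follow-up investigator nor the endpoint committee is stated to be masked

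*Protocol article*

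**What the plan says.** The limitations paragraph at the end of section 3.2.2 of the protocol article lists measurement bias as its second concern. It gives the source as follows: "both the proficiency of the assessors and the way of questioning may affect the assessment’s reliability, leading to measurement bias". The remedy comes next: "Therefore, we will conduct uniform training for the assessors to avoid it".

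Other sections describe who ascertains outcomes:

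- **Primary outcome (2.4):** "The primary outcome is a composite of 90-day all-cause mortality or readmission for HF".
- **Follow-up (2.6.2):** within seven days of each visit time point, "an independent investigator will confirm survival status, HF readmission, NYHA cardiac function classification, MACE, and AEs of patients by telephone or outpatient".
- **Adjudication (2.5):** "The MACE endpoints and cardiac-specific death will be assessed and determined by the endpoint committee".
- **MACE definition (2.4):** "MACE is defined as any of the following: death, MI, stroke, hospitalization because of HF, and revascularization".
- **Exposure record (2.5):** "The use of YQFM will be evaluated based on the daily medication record".

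Treatment is at the physicians' discretion (2.3). The only mention of double-blinding, in the Introduction, concerns the separate AUGUST-AHF RCT.

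**The concern.** Measurement error comes in two kinds. If its size and direction are the same in both groups, it mostly adds noise, and training reduces it. If it depends on exposure, it shifts the effect estimate, and training does nothing about it: two perfectly trained assessors can both lean the same way when they know who received YQFM. Section 3.2.2 describes only the first kind, yet presents training as enough to avoid measurement bias.

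In an open comparative cohort the second kind matters more. Deciding whether a readmission was for HF takes judgement, and that decision is half of the primary composite. NYHA class and cardiac cause of death also take judgement, although they affect secondary outcomes only.

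Two things are at stake. First, the analysis in section 2.8 cannot repair this error. Propensity-score matching balances baseline variables, and the Rosenbaum sensitivity analysis addresses unobserved confounding; neither deals with misclassified outcomes. Second, Objective 2 compares this cohort with a double-blind RCT on the same primary outcome. Differential ascertainment in the cohort could be read there as a real-world difference in effect.

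**Working it through.** **Step 1. What each safeguard covers.**

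| Outcome | Who judges it, per the article | Open to exposure-dependent judgement? | Masking stated? |
|---|---|---|---|
| All-cause death (primary component) | Independent investigator confirms survival status (2.6.2) | No | Not needed |
| HF readmission (primary component) | Independent investigator (2.6.2); HF hospitalization is also a MACE component (2.4), and MACE goes to the committee (2.5) | Yes | No |
| NYHA class at follow-up | Independent investigator, by telephone or outpatient (2.6.2); no committee review | Yes | No |
| Cardiac-specific death | Endpoint committee (2.5) | Yes, as to cause | No |

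Two gaps follow. Independence and committee review are not the same as being unaware of exposure. And although HF hospitalization can reach the committee as part of MACE, no section says that the committee's ruling is the one counted in the primary outcome.

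**Step 2. The plan's own figure.** Inputs from section 2.7: 25% versus 18%, two-sided alpha 0.05, 80% power, 10% loss. Equal groups are assumed, because no ratio is stated. With the pooled-variance formula for two proportions,

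n = [1.960·√(2·0.215·0.785) + 0.842·√(0.25·0.75 + 0.18·0.82)]² / 0.07² = 539.5, so 540 per group.

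2 × 540 = 1,080, and 1,080 / 0.90 = 1,200. The stated 1,200 is reproduced and is not in dispute.

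**Step 3. Illustration of size.** The control rate is documented: "the composite outcome of 90-day all-cause mortality or readmission for HF was approximately 25% among patients who received conventional therapy". The rest is assumed:

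- no true effect, so the true risk is 25% in both groups;
- h, the part of that 25% made up of HF readmissions, is 15 or 20 percentage points;
- f, the fraction of exposed-group HF readmissions labelled non-HF, is 5%, 10% or 20%, with no such error in the unexposed group;
- 540 analysed per group, two-sided z test for two proportions.

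Observed exposed rate = 25% − f·h. With d = f·h, and s₀ and s₁ the pooled and unpooled standard errors of the difference, the rejection probability is Φ[(d − 1.96·s₀)/s₁] + Φ[(−d − 1.96·s₀)/s₁].

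| f | Observed exposed rate, h = 15 | Chance of p < 0.05 | Observed exposed rate, h = 20 | Chance of p < 0.05 |
|---|---|---|---|---|
| 0 | 25.00% | 5% | 25.0% | 5% |
| 5% | 24.25% | 6% | 24.0% | 7% |
| 10% | 23.50% | 9% | 23.0% | 12% |
| 20% | 22.00% | 21% | 21.0% | 35% |

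Worked line (f = 10%, h = 15): d = 0.015 and s₀ ≈ s₁ ≈ 0.0261. The first term is Φ(−1.385) = 0.083 and the second 0.006, together 0.089.

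To produce the whole assumed 7-point difference, mislabelling would have to reach 7/20 = 35% to 7/15 = 47% of exposed-group HF readmissions. Small error rates therefore do modest harm, and only large ones would imitate the full planned effect.

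**The case against.** The case on the other side has four parts.

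- **Training is not the only safeguard.** A reader of section 3.2.2 alone might infer that it is. Sections 2.5 and 2.6.2 do not support that: cause of death goes to a committee, HF hospitalization can reach the same committee through MACE, and the follow-up investigator is independent. This part stands fully. What remains is that neither role is stated to be masked.
- **The training sentence answers a narrower problem.** It concerns assessor skill and questioning, for which training is apt, and the paragraph opens by conceding that bias could hardly be eliminated. This stands in part. The remedy fits the source named, but the claim to avoid measurement bias is still too strong when the exposure-dependent source goes unmentioned.
- **Masking may be described elsewhere.** A journal article condenses a fuller protocol, and adjudication procedures often sit in a charter. A reader might infer that the investigator and the committee know each patient's YQFM status. The article does not say so; it is an inference from the open design and the daily medication record. Silence does not prove that masking is absent.
- **The magnitude rests on assumptions.** This stands. The article supports neither the share of HF readmissions nor any mislabelling rate. The error was taken to run in one direction and in one group only; the opposite direction would hide a benefit instead of creating one. The planned analysis is also a matched Cox model, not a comparison of two proportions.

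**Conclusion.** The point holds in a limited form. Training addresses reliability, not judgement that differs by known exposure, so section 3.2.2 overstates the protection. The two roles that could supply the missing protection already exist, but as written neither is masked to YQFM, and the link from committee adjudication to the primary outcome is left open. HF readmission, NYHA class and cause of death are exposed to this; all-cause death is not.

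No bias of a known size has been shown. Under the stated assumptions the false-positive rate rises from 5% to 6–7% at 5% mislabelling, 9–12% at 10% and 21–35% at 20%. These figures show sensitivity and are not estimates. The change is worth making because it costs little and protects both the primary outcome and the comparison with the double-blind RCT. It does not call the design or the sample size into question.

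**What to change.** 1. **Section 2.6.2:** state that the independent investigator classifies HF readmission and NYHA class without access to in-hospital YQFM data.
2. **Section 2.5:** state that the endpoint committee adjudicates HF readmission for the primary outcome, as well as MACE and cardiac-specific death, from files with YQFM entries removed.
3. **Section 3.2.2, limitations paragraph:** confine the training claim to reliability, and cite masking as the safeguard against differential assessment.

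If a fuller protocol or committee charter already provides for masking, a sentence saying so replaces items 1 and 2 as far as it covers them.

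The cost is wording and a small amount of redaction. Both roles already exist, so no new ones are needed. Some patients will reveal their treatment during a call or visit, so masking will be incomplete.

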## Ethics statement

The studies involving human participants were reviewed and approved by Ethical Committee of Dongzhimen Hospital. The patients/participants provided their written informed consent to participate in this study.
